**Patients:**

*Study 1:*

*Uncomplicated falciparum malaria (UF)*:

Inclusion criteria:

1. age 18-60 years
2. *P. falciparum* parasitemia (1,000-100,000 parasites/ul).
3. Clinical syndrome consistent will malaria associated with documented fever (axillary temperature  38oC) or self-reported history of fever in the last 48 hours with no other cause present
4. Time of commencement of quinine known
5. An indication for hospital admission [eg relative cannot stay at home to look after them or supervise their treatment at home, one episode of vomiting (but not repeated episodes of vomiting)], but not having the warning signs or severe malaria criteria in “exclusion criteria” below
6. Informed consent obtained

Exclusion criteria:

1. pregnancy or lactation
2. mixed infection with *P. falciparum* and *P. vivax*
3. warning signs ofaltered mental state and inability to sit unaided
4. features of severe/complicated malaria2 (see “severe malaria” below)
5. diabetes
6. systolic BP <100 mmHg
7. serious underlying diseases (cardiac, hepatic, kidney and lung)
8. malnutrion
9. other infection
10. concurrent therapy/medication including: anti-TB, Asthma drugs.

All UF subjects will be treated with quinine as per standard RSMM practice. Height and weight will be documented in all subjects.

*Severe malaria (SM)*, defined by modified WHO criteria42:

Inclusion criteria:

1. age ≥ 18 years
2. Informed consent obtained
3. Time of commencement of quinine known
4. any level of *P. falciparum* parasitemia, and one or more of the following criteria:
   1. acute renal failure (creatinine >265umol/L)
   2. hyperbilirubinemia (total bilirubin > 50 umol/L) with either renal impairment (creatinine > 130umol/L) or parasitemia of >100,000 parasites/uL
   3. blackwater fever
   4. hyperparasitemia (>10% parasitised red cells)
   5. cerebral malaria (Glasgow coma score <11)
   6. Hypoglycemia
   7. Respiratory distress (RR>32)
   8. Acidosis: venous bicarbonate < 15 mmol/L.
   9. Shock: systolic BP <80 mmHg with cold peripheries

Exclusion criteria:

1. severe anemia (Hb <6 mg/dL) and
2. pregnancy or lactation.

Clinical care, and monitoring will be as per standard national, RSMM and WHO protocols2.

*Studies 2 and 3: Uncomplicated falciparum malaria (UF)*:

Inclusion criteria:

1. age 18-60 years
2. *P. falciparum* parasitemia (1,000-100,000 parasites/ul).

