- *Effect on K+:* Hyperkalemia may result from redistribution of K+ from intracellular fluid to extracellular fluid. In seven of eight normal Italian subjects receiving high dose arginine (30g IV), mean plasma K+ transiently increased by 1.23± 0.17 meq/L (range 0.6-1.7), peaking at 60-90 mins after start of a 30 min IV infusion54. These data excluded one subject who had a “virtually negligible” increase54. Clinically significant hyperkalemia has been reported with large supraphysiological doses in patients with renal failure (30g IV)55 and combined liver failure/renal impairment (again with very high dosing of 59-95g IV)56, in subjects taking spironolactone (an exclusion criterion in this study). Mean plasma K+ in 58 Indonesian subjects with uncomplicated malaria (in our initial NO studies in Jayapura) is at the low end of normal range (3.4 meql/L), with only 1 subject out of 58 having a K+> 4.0 [4.5 meq/L]. Subjects with renal failure or baseline K+≥4.2 meq/L will not be included in studies 2 and 3. Moreover lower doses will be used in both of our studies than the 30g dose used in published studies. Therefore a rise in K+ to ≥ 6.0 meq/L will be very unlikely.

Response: If serum K+ rises to ≥ 6.0 meq/L it will be immediately repeated using the bedside iSTAT to exclude hemolysis of sample. If K+ ≥ 6.0 meq/L or if significant ECG changes of hyperkalemia develop, the infusion will be stopped and subjects will be given 10ml of 10% calcium gluconate for membrane stabilization. This will be followed by continuous ECG monitoring and 10-15 minutely monitoring of K+: if thought necessary by the attending clinician, 10 U of regular insulin will be administered with 25g of IV glucose to induce K+ shift into cells.

- *Hypophosphatemia:*

A clinically insignificant transient fall in serum phosphate is noted with 30g infusions, with the maximum fall below baseline of 1.11 mg/100ml (or 33%), peaking 60 mins after commencement of a 30 min infusion54. In no cases did phosphate levels fall to potentially clinically significant levels (<1 mg/dL)54. We will nevertheless measure phosphate levels at baseline and at 60 mins.

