*d) Consequences of tissue NO production from tissue NOS.* We believe that tissue NO production will have tissue-protective effects and will also reduce generation of superoxide from arginine-deficient NOS. Nevertheless we will be able to detect unexpected deleterious effects of increased tissue NO. As well as the organ-specific biochemical markers above (including creatinine, creatine kinase and liver enzymes/bilirubin), our existing lung function laboratory at RSMM and the exhaled NO apparatus will give us the unique opportunity to relate exhaled NO to measures of pulmonary gas transfer and alveolar dead space, sensitive markers of lung injury.

In the current sickle cell disease trial in the US children with acute vaso-occlusive disease, 36 patients (age 4-18 years) have been randomized to IV arginine 0.1 g/kg vs placebo. This has been very well tolerated, with no significant effect on blood pressure, liver function tests, electrolytes, glucose, renal function or vital signs ([name], personal communication 2004). There have been no serious adverse events, and no acidosis

**Serious adverse events:** The following adverse events will be deemed serious, and will be notified immediately to the Chief Investigators and to the Chair of the Data Monitoring Committee for immediate review:

1. Death
2. Serum K+ rising > 6.0 meq/L with ECG changes
3. Anaphylaxis
4. SBP falling below 80 mmHg unresponsive to saline infusion
5. Clinical requirement for admission to High Care Unit, dialysis or ventilation

The doctor responsible for immediate management of adverse effects will be the internal medicine residents from Manado, currently [name]. These are very experienced senior internal medicine residents.

**Limitations of Study 1 and 2:** Only patients with Hb≥6g/dl are included in this study. We do not believe that the PK-PD relationship will be significantly different in severe malarial anemia than in other forms of severe malaria, but cannot exclude this. Once the PK-PD relationship in severe malaria is known, in future studies we may be able to confirm its similarity in severe malaria anemia with fewer blood draws.

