***Ethical issues:***

*Potential side effects of arginine:* Patients with uncomplicated malaria have mean levels of arginine *below* normal, and combined with a dose well below the standard 30g IV dose used in other settings, we do not expect significant adverse effects to occur. Whilst we believe adverse effects to be unlikely, our protocol outlined in “study 2” above allows us to detect, and if necessary rectify them:

*Standard treatment:* Regardless of whether they receive arginine, all patients will receive prompt standard antimalarial drug treatment based on standard Depkes and RSMM protocols, currently quinine. There will be no delay in starting treatment due to participation in this study.

*Blood samples:* the maximum total of 25ml of blood taken over 21-72 hours is safe. Those with significant anemia (Hb <6 g/dL) will be excluded. Serial sampling is essential for appropriate pharmacokinetic-pharmacodynamic modeling. However serial blood sampling has the potential to cause concern to patients. In northern Australia, we have successfully used flip charts during the consent process to illustrate visually the procedure of studies like this that involve blood sampling. We will use similar flip charts to demonstrate visually the total volume of blood that will be collected. The flip chart will illustrate that the very small volumes collected during serial bleeds add up to only a relatively small and safe volume of blood. The use of these flip charts have proved to be especially useful in explaining blood volumes in patients with limited education who have limited numeracy and literacy skills.

*Cannula:* The consent process will explain how the cannula will be the same as that used clinically for medications and fluids. The information process will clarify that the cannula will ensure that the serial samplings will be painless and avoid the need for further painful needlesticks or fingerpricks. We will also explain that the blood taken from the cannula will also be used for any serial clinical tests requested by the treating RSMM doctor (eg repeat parasite counts, blood glucose, repeat hemoglobin), thus avoiding painful followup fingerpricks required for clinical purposes. Moreover, the serial iSTAT readings will be useful to the treating doctor, who will be alerted to abnormal results of clinical importance.

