| Phosphate ** |  | X |  |  |  |  | X | X | X | X | X | X | X |  |
| Thick/thin film* | X | X |  |  |  |  |  |  |  |  | X | X | X | X |
| Lactate at RSMM* |  | X |  |  |  |  |  |  |  |  | X |  | X |  |
| LFTs, CK, Creatinine** |  | X |  |  |  |  |  |  |  |  |  | X | X | X |
| Exhaled NO* |  | X |  |  |  | X | X | X | X | X | X | X | X | X |
| Gas transfer (DLCO)* |  |  |  | X |  |  |  |  | X |  |  |  | X | X |
| Physiological dead space* |  | X |  |  |  |  |  |  | X |  |  |  | X |  |
| Endothelial function testing* |  |  | X |  |  |  |  | X |  |  |  |  | X | X |
| Amino acids (incl. arginine), NOx, ICAM, oxidant markers** | X | X |  |  |  | X | X | X | X | X | X | X | X | X |
| Urine (pterins, NOx)** |  |  |  | X |  |  |  |  |  |  | X*** |  | X*** | X |

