# iSTAT EC8+ is a bedside biochemistry cartridge which uses only several microlitres to measure Na+, K+, Cl-, pH, PCO2, urea nitrogen (BUN)/urea, glucose, hematocrit, TCO2, bicarbonate, Base excess, anion gap, hemoglobin.

ECG will be monitored continuously for up to 6 hours after arginine infusion and repeated at 20 hours. Temperature will also be monitored 4-6 hourly until 20 hours.

‡ Clinical symptom and sign assessment: questioned on presence of headache, lightheadedness, nausea, vomiting, flushing, numbness, difficulty breathing, pain at infusion site; and examined for rash.

Location of each testing procedure: A strength of this study is that all the endothelial physiology measurements, all the lung physiology measurements, all the parasite counts, the lactate and phosphate measurements, and most of the other biochemical measurements (eg iSTAT bedside biochemistry) will be undertaken **on site** at RSMM in Timika (either at the bedside or at the RSMM lab), with on-the-job training of all local and visiting staff involved. The asterisks (* or **) identify which measurements will be done at RSMM in Timika (*) and which at MSHR (**) or University of Sydney (oxidant stress measurements).

*performed at RSMM.

** performed in Darwin

*** Urine will be collected at approx 4 hours, and at each time voided thereafter.

§ if patient still in hospital

§§ in severe malaria patients only

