**APPENDIX 1 List of Abbreviations**

ATS: American Thoracic Society

CAT 1: Cationic amino acid transporter 1

CAT 2: Cationic amino acid transporter 2

CK: Creatine Kinase

CL: Clearance

Cl-: Chloride

CM: Cerebral Malaria

DLCO: Lung diffusion for carbon monoxide, a measure of Gas Transfer

FMD: Flow mediated dilatation

GMP: Good Manufacturing Practice

GSH: Plasma glutathione

GSSG: Oxidised Glutathione

HCO3-: Bicarbonate

iSTAT: Brand of Portable Clinical Analyzer

K+: Potassium

Km: Equilibrium constant

LFTs: Liver Function Tests

MSHR: Menzies School of Health Research

NIHRD: National Institute for Health Research and Development

NONMEM: Computer software program to model non-linear pharmacokinetics of drugs.

NO: Nitric oxide

NOS1: Nitric oxide Synthase 1 or Neuronal Nitric oxide Synthase

NOS2: Nitric oxide Synthase 2 or Inducible Nitric oxide Synthase

NOS3: Nitric oxide Synthase 3 or Endothelial Nitric oxide Synthase

NOx: Nitric oxide metabolites, nitrate plus nitrite

PBMCs: Peripheral blood mononuclear cells

PK: Pharmacokinetic (change in arginine concentration over time)

PD: Pharmacodynamic (change in arginine effect over time)

RSMM: Rumah Sakit Mitra Masyarakat

sICAM-1: soluble intercellular adhesion molecule 1

SEAQUAMAT: South East Asian multi-center study of QUinine versus Artesunate for severe MAlaria Trial.

SM: Severe *Plasmodium falciparum* Malaria

SCD: Sickle Cell Disease

VOCS: Vaso-occlusive syndrome (found in SCD)

UF: Uncomplicated *Plasmodium falciparum* malaria

WHO: World Health Organization

Appendix 2

Table of Laboratory Tests to Be Done and Location Where Tests Will be Performed

| Type Of Specimen | Tests To Be Performed | Location of Tests |
| --- | --- | --- |
| Whole Blood | ISTAT EC8-(Glucose, Sodium, Potassium, Chloride, Urea, Hematocrit, Hemoglobin, PH, Base Excess, Anion Gap, Total CO2, PCO2) | RSMM-Timika |
| Whole Blood | Thick and Thin Films for Malaria parasites | RSMM-Timika |
| Whole Blood | Lactate, Phosphate | RSMM-Timika |
| Plasma | Liver function tests, Creatinine, creatine kinase | RSMM-Timika  Cross Checked in Darwin |
| Plasma | Arginine, other amino acids, NOx, ICAM-1 | MSHR, Darwin with participation of NIHRD scientist |
| Whole blood/Plasma | Markers of Oxidative Stress (incl. GSH:GSSG and cell superoxide release) | University of NSW, Sydney |
| Plasma | Endothelial microparticles | University of Marseille,  France |
| Urine | NO metabolites and Pterins | MSHR, Darwin |

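### Two safety exclusions the text relies on, Hb below 6 g/dL and renal failure, are not carried consistently into the eligibility lists and the test tables

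*Combined protocol and SAP*

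**What the plan says.** **Haemoglobin.** Limitations of Study 1 and 2: "Only patients with Hb≥6g/dl are included in this study". Ethical issues, Blood samples, in support of the safety of serial sampling: "Those with significant anemia (Hb <6 g/dL) will be excluded". In the Patients section, the criterion appears only among the Study 1 severe malaria exclusions, as "severe anemia (Hb <6 mg/dL" (closing bracket dropped here). The Study 1 UF list and the Studies 2 and 3 list do not contain it.

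**Renal function.** Under Effect on K+, the protocol argues that a potassium of 6.0 meq/L or more is very unlikely, partly because "Subjects with renal failure or baseline K+≥4.2 meq/L will not be included in studies 2 and 3". The Studies 2 and 3 list reaches renal failure by two routes: exclusion 4, which points to the Study 1 severe malaria criteria, and exclusion 7, serious underlying kidney disease.

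**Where the tests are run.** The Table 2 row "LFTs, CK, Creatinine" carries a double asterisk, which the footnotes define as "performed in Darwin". Appendix 2 lists "Liver function tests, Creatinine, creatine kinase" at RSMM-Timika with a cross-check in Darwin. The EC8+ cartridge description ends with "urea nitrogen (BUN)/urea, glucose, hematocrit, TCO2, bicarbonate, Base excess, anion gap, hemoglobin"; creatinine appears nowhere in it. Under Effect on kidney function, the protocol nevertheless plans to follow renal function by serial bedside iSTAT.

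**The concern.** Staff enrol from the eligibility lists and sample from the tables. If those pages do not carry an exclusion that the safety or ethics text promises, a patient whom the committees were told is excluded can be enrolled without any protocol deviation.

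For Hb, the promise supports the claim that drawing up to 25 ml is safe. For renal failure, it supports the hyperkalaemia argument: the same paragraph reports clinically significant hyperkalaemia at 30 g in renal failure, and at 59-95 g in combined liver failure and renal impairment. If creatinine is assayed off site, the exclusion could be checked against its own laboratory definition only after dosing.

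**Working it through.** No sample size, power or error rate is involved. The check sets the sections side by side, with a little arithmetic.

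1. **Hb, list by list.**
   - Study 1 UF exclusions (items 1-10): no Hb criterion.
   - Studies 2 and 3 exclusions (items 1-10): no Hb criterion. The iSTAT limits in item 8 cover glucose, K+, Cl- and HCO3- only.
   - Both lists refer to the Study 1 severe malaria criteria. The nine criteria printed there do not include anaemia.
   - Study 1 severe malaria exclusions: present, in mg/dL. Since 6 mg/dL = 0.006 g/dL, the printed figure is 6 / 0.006 = 1,000 times below the 6 g/dL given in the two narrative sections.

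2. **Is Hb measured in time?** In Study 2, yes. The EC8+ panel includes haemoglobin and is run on the sample taken 60 minutes before infusion. Study 3 baseline sampling follows Study 2. The criterion is missing, not the measurement.

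3. **Patients under lists without the Hb criterion who are serially bled.** Study 1 UF: 20. Study 2: 10 + 10 + 10 = 30. Study 3: about 20 + 20 = 40. Total about 90. The further 30 Study 1 uncomplicated patients have admission-only physiological and exhaled NO measures and are not counted.

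4. **What exclusion 4 needs.** Acute renal failure is defined as creatinine above 265 umol/L. The hyperbilirubinaemia criterion needs bilirubin above 50 umol/L with either creatinine above 130 umol/L or parasitaemia above 100,000/uL. UF entry caps parasitaemia at 100,000/uL, so for these patients the second criterion also comes down to creatinine, together with bilirubin.

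5. **When is a creatinine result available?** Table 2 draws it at -60 minutes, 480 minutes, the next morning and 1-2 weeks, with none in the clinic-sample column. Infusion runs from 0 to 30 minutes.
   - By Table 2 and its footnote, the assay is in Darwin, so there is no result at time 0.
   - By Appendix 2, the assay is in Timika, so a result within the 60 minutes is possible. No turnaround time is given, and nothing ties the result explicitly to the start of infusion.
   - By bedside iSTAT, urea is available at -60 minutes, but no exclusion is written in terms of urea.
   - Study 1 sampling text lists creatinine and LFTs for later assay on frozen plasma. Study 2 sampling text names creatinine only in the final 20-hour safety set.

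6. **How much the potassium argument rests on the renal exclusion.** Baseline K+ must be below 4.2, and the largest rise cited at 30 g is 1.7. The peak is then below 4.2 + 1.7 = 5.9, which leaves at least 6.0 - 5.9 = 0.1 meq/L. At the reported means, 3.4 + 1.23 = 4.63. The rise comes from normal subjects, so neither sum describes a patient in renal failure. Planned Study 2 doses (3-12 g, possibly up to 18 g) are below 30 g, which adds margin.

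7. **Arginine recipients affected by the creatinine conflict.** 30 in Study 2 plus about 20 in Study 3, about 50.

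**The case against.** A reader might infer that neither exclusion can be applied before infusion. The documents do not support that.

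- Hb is on the bedside panel an hour before dosing.
- Appendix 2 allows an on-site creatinine. Study 1 enrols severe malaria on creatinine criteria, and the Feasibility text describes staff experienced in assessing them.
- Exclusion 7 can be applied on history. Study 3 allocates a code only to patients with no exclusion criterion, so eligibility must be settled first.
- The double asterisks are unreliable elsewhere. Phosphate carries them in both tables, while the footnotes and Appendix 2 place it on site.
- A sampling schedule does not show that routine admission tests are omitted.

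A reader might also infer that the hyperkalaemia safeguard collapses. It does not. The protocol gives other reasons: the baseline K+ limit, low observed K+ (1 of 58 above 4.0), the spironolactone exclusion and lower doses. Table 2 repeats the bedside panel during and after infusion, with ECG monitoring.

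On Hb, the mg/dL figure is plainly a misprint. The Limitations text treats severe malarial anaemia as a form of severe malaria, so exclusion 4 with its cited reference could be read to cover it.

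All of this stands against the stronger readings. It does not remove the contradictions. An implied route through a cited reference is not a listed criterion, and an unreliable asterisk leaves staff unable to tell which location governs. That Study 3 requires exclusions to be absent does not say which result shows it.

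**Conclusion.** The concern holds as a failure to carry two stated exclusions consistently into the lists and tables. The Hb exclusion is missing from the UF lists covering about 90 serially bled patients and is misprinted in the only list that has it. The renal exclusion is listed, but its laboratory basis has two conflicting locations: under one, about 50 arginine recipients have no creatinine result at time 0; under the other, they can.

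These counts are patients enrolled under the inconsistent text, not patients wrongly enrolled; the documents do not say how many UF patients would have Hb below 6 g/dL or creatinine above 265 umol/L. The Study 3 figures are the protocol's provisional estimate, and any additional 18 g cohort in Study 2 is not counted. The conclusion assumes that staff follow the lists and tables as printed. It should be settled before enrolment, because a safety premise and an ethics assurance depend on it and the correction is cheap.

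**What to change.** 1. Reconcile the Patients section with Limitations of Study 1 and 2 and with Ethical issues. Either carry the stated Hb exclusion into the Study 1 UF list and the Studies 2 and 3 list, or withdraw the assurance from the narrative. Correct the unit in the Study 1 severe malaria list.
2. Reconcile Tables 1 and 2 and their footnotes with Appendix 2, with Effect on K+ and with Effect on kidney function. The location and timing of the tests behind the stated renal exclusion should be consistent with applying it before infusion, and the text should say what the bedside panel contributes. Correct the phosphate marks at the same time.

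The cost is edits to lists, tables and footnotes, with notice to the ethics committees if an assurance changes. If the reconciled text has creatinine reported on site first, the arginine start would wait for that result. The commitment that antimalarial treatment is not delayed would be unaffected. Which threshold or clinical rule applies is for the sponsor and the investigators; none is proposed here.
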